### Outcome measures

The primary outcome measure is the EQ-5D-5L at 12 weeks postrandomisation.

Secondary outcome measures are:

Two and 6 weeks: EQ-5D-5L, Neck Disability Index (NDI), Neck Numeric Pain Scale.Twekve weeks: NDI, Neck Numeric Pain Scale, adverse events (AEs), compliance with hard collar use, analgesia use, length of hospital stay, discharge destination, bony fusion/stability on imaging, loss of muscle bulk in upper limbs using grip strength and bioimpedence.Six and 12 months: EQ-5D-5L, NDI, Neck Numeric Pain Scale, injury-related complications, mortality, health and social care visits/use, hospital admission or outpatient visits, health economics analysis.

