### Trial assessments

Assessments and timing of data collection are shown in table 1. Baseline data on demographics, comorbidities, injury, radiological findings and inpatient management will be recorded. Patient diaries will be used to collect pain scores, analgesia and collar use. Standard local clinical follow-up will occur. Research assessments will be carried out at 2, 6 and 12 weeks by the local research team and by a blinded member of the central research team at 6 and 12 months. Assessments will occur via telephone interviews, postal or online questionnaires, or during standard care appointments. A proxy can provide information on a patient’s behalf when required. Up to three reminder telephone calls will be made to maximise completion.

**Table 1 T1:** Timing of study assessments

	Timing from randomisation						
	Baseline	Discharge	2 weeks	6 weeks	12 weeks	6 months	12 months
Assessment							
Eligibility assessment	*						
Consent	*						
Demographics							
Baseline data	*						
CFS^23^	*						
Imaging							
Fracture type	X						
Imaging type	X				X		
Outcomes							
EQ-5D-5L			*	*	*	*	*
EQ-VAS			*	*	*	*	*
Neck Numeric Pain Scale			*	*	*	*	*
NDI			*	*	*	*	*
AEs		*			*		
Injury-related complications						*	*
Collar use		*	*	*	*		
Grip strength/bioimpedance	*				*		
Service use			*	*	*	*	*
Analgesia use			*	*	*		
Mortality					*	*	*

Assessments undertaken as standard care are shown with x. Study specific assessments are shown with*. Assessments may occur within the following time windows: 2 weeks (±1 week), 6 and 12 weeks (±2 weeks) and 6 and 12 months (±4 weeks). Fracture type refers to that of Anderson and D’Alonzo.^24^

EQ-5D-5L - EuroQol 5 dimension instrument 5 level version

AEs, adverse events; CFS, Clinical Frailty Scale; NDI, Neck Disability Index; VAS, Visual Analogue Scale.

At centres with facilities for routine assessment of grip strength and bioimpedence, all participants will be invited to take part in this arm of the study. Loss of muscle bulk in the upper limbs will be assessed over 12 weeks using hand grip strength measured with a dynamometer.^27^ Bioimpedence measurements will be made at the wrist and ankle. Muscle mass and skeletal muscle index as a marker of frailty will be calculated as per Janssen *et al.*^28^

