### Data analysis plan

The primary data analysis will be by intention to treat. A 5% two-sided significance level will be used throughout. A detailed statistical analysis plan will be developed by the study statisticians and finalised prior to locking of the trial database.

Analysis of the primary outcome will be a repeated measures analysis of covariance, including terms for treatment arm and the EQ-5D-5L responses at 2, 6 and 12 weeks. Adjustments will be made for the variables included in the randomisation minimisation algorithm. Adjustment for study site will be included as a random effect, if appropriate. The repeated measures approach enables estimation of an intervention effect at week 12 postrandomisation (primary outcome), and an overall assessment of the effect of the intervention over the 12-week period.

The 12-week NDI and Visual Analogue Scale will be analysed in a similar manner to the EQ-5D-5L. It is anticipated that results will underpin any between group differences seen in EQ-5D-5L, confirming and strengthening the clinical interpretation of the findings. All other secondary outcomes will be analysed with statistical models appropriate to the distribution of the outcome (see table 3). Where there are data recorded on multiple occasions postrandomisation, we may use an appropriate repeated measures model. Exploratory subgroup analyses by fracture type (I, II and III),^24^ CFS (<5 vs ≥5)^23^ and age (<75 vs ≥75 years) will be performed. The influence of any missing data on the robustness of the findings will be examined, for example, using multiple imputation models under a missing at random assumption. Screening logs will be analysed to assess generalisability of results.

**Table 3 T3:** Possible methods of analysis

Variable	Hypothesis	Outcome measures	Analysis methods
Baseline data	No difference between groups	Gender, age, comorbidities, injury data, radiological findings, inpatient management, CFS	Categorical variables: absolute numbers and percentages. Continuous variables: mean, median, SD, IQR.
Primary outcome			
Health-related quality of life at 12 weeks	Clinically important difference between two groups with early collar removal superior	EQ-5D-5L (continuous)	Repeated measures analysis of covariance at 2, 6 and 12 weeks, adjusting for minimisation variables
Secondary outcomes			
Pain	No difference between groups	NPRS (ordinal)	Ordinal regression

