Function	No difference between groups	EQ-VAS (continuous), NDI (continuous) Grip strength (continuous) Bio impedance (ordinal)	Repeated measures analysis of covariance at 2, 6 and 12 weeks, adjusting for minimisation variables Student t-test Nonparametric methods; Mann-Whitney, Wilcoxon signed ranks test
Mortality	No difference between groups	All-cause mortality (binary)	Logistic regression, Χ^2^
Collar use	Significantly greater in the collar group	No of days of collar use (continuous)	Poisson regression
Health economics	Baysian assessment of likelihood incremental cost per QALY of either arm is below NICE Thresholds (£20 k to £30 k per QALY)	Service use & cost, QALYs (adjusted from EQ-5D-5L) Incremental Cost Per QALY	Generalised linear lodelling of cost and QALYs. Probabilistic sensitivity analysis via recycled predictions
Sub-group analysis;			
Fracture type (I, II and II)	No difference		For each analysis, the subgroup variable and interaction term between intervention and subgroup variable will be included in the model.
CFS (<5 vs ≥5)	Better treatment effect in CFS ≥5		
Age (<75 vs ≥75 years)	Better treatment effect in age ≥75		

Methods to be used for analysing variables collected in the DENS study. A detailed statistical analysis plan will be published.

CFS, Clinical Frailty Scale; DENS, Duration of External Neck Stabilisation; NDI, neck disability index; NICE, National Institute for Health and Care Excellence; NPRS, Numeric Pain Rating Scale; QALY, quality-adjusted life year; VAS, Visual Analogue Scale.

Interview data will be analysed thematically using the method of constant comparison. To ensure rigour, several individuals will be involved in data analysis and coding. An interactive working group will be set up, comprising the qualitative research team, co-investigators, the trial manager, patient and public involvement (PPI) representatives, and at least one healthcare professional from each of the sites involved in the pilot phase. A ‘what, so what, now what’ approach^32^ will be used to translate qualitative findings and other experiences shared by group members into tangible recommendations.

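### Table 3 names only unadjusted tests for grip strength and bioimpedance, leaves the use of baseline open, calls bioimpedance ordinal, and lists a paired test under a between-group hypothesis

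*Protocol article*

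**What the plan says.** The Outcome measures section lists among the 12-week secondary outcomes "loss of muscle bulk in upper limbs using grip strength and bioimpedence". The Trial assessments section adds: "Loss of muscle bulk in the upper limbs will be assessed over 12 weeks using hand grip strength measured with a dynamometer". Of bioimpedance, measured at wrist and ankle, it says: "Muscle mass and skeletal muscle index as a marker of frailty will be calculated". Only centres with the facilities take part in this component, and no sample size is given for it.

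In Table 1, the line "Grip strength/bioimpedance" carries a study-specific mark at baseline and at 12 weeks. It is the only line under Outcomes with a baseline mark; EQ-5D-5L, EQ-VAS, NDI and the pain scale have none.

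Table 3 is titled "Possible methods of analysis". Its Function row has the hypothesis of no difference between groups. After EQ-VAS and NDI it lists "Grip strength (continuous) Bio impedance (ordinal"). The methods cell gives a repeated measures analysis of covariance adjusted for the minimisation variables, followed by "Student t-test Nonparametric methods; Mann-Whitney, Wilcoxon signed ranks test". The Data analysis plan also states: "A detailed statistical analysis plan will be developed by the study statisticians and finalised prior to locking of the trial database".

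**The concern.** There are four separate points in one table row.

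- **No covariates.** These are the only outcomes in Table 1 with a scheduled pre-treatment measurement, yet the listed tests adjust for neither that value nor the minimisation variables. EQ-VAS and NDI, in the same row, are adjusted for the minimisation variables.
- **Variable not fixed.** The text speaks of loss over 12 weeks, but Table 3 does not say whether the t-test and Mann-Whitney test are applied to 12-week values or to changes from baseline. The two choices can differ a good deal in precision.
- **Measurement scale.** An ordinal label does not fit a measurement from which muscle mass and an index are calculated. No ordered categories are defined anywhere in the article.
- **Test and hypothesis do not match.** A signed-rank test pairs a participant's two values and tests change over time. It gives no comparison of the arms.

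What is at stake is precision in a component restricted to equipped centres, and the reading of any within-arm p-value. Change that is significant in one arm and not in the other is not evidence of a treatment effect.

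**Working it through.** **The plan's own figures.** No sample size or power is stated for grip strength or bioimpedance. The stated sample size concerns EQ-5D-5L and reproduces: 1514/0.8 = 1892.5, rounded up to 1893, and 1893 × 0.75 × 0.625 = 887.3, stated as 887. It is not in dispute. One step of it is relevant here: a covariate correlation of 0.5 is said to allow a 25% reduction, and 1 − 0.5² = 0.75. So the Sample size section already uses the variance formula applied below.

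**Inputs.** One baseline and one 12-week value per participant (Table 1). A two-sided 5% level (Data analysis plan). The baseline to 12-week correlation r of these measures is not in the document and is assumed over a range. Equal variances at the two times are also assumed.

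**Formulas.** Take the variance of a comparison of 12-week values alone as 1.

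- ANCOVA on the baseline value: 1 − r².
- t-test on change: 2(1 − r).
- Participants needed relative to ANCOVA, t-test on 12-week values: 1/(1 − r²).
- Participants needed relative to ANCOVA, t-test on change: 2(1 − r)/(1 − r²) = 2/(1 + r).

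| Assumed r | ANCOVA variance | Change variance | 12-week t-test vs ANCOVA | Change t-test vs ANCOVA | Power of 12-week t-test where ANCOVA has 80% |
|---|---|---|---|---|---|
| 0.5 | 0.75 | 1.00 | 1.33 | 1.33 | 68% |
| 0.7 | 0.51 | 0.60 | 1.96 | 1.18 | 52% |
| 0.8 | 0.36 | 0.40 | 2.78 | 1.11 | 39% |
| 0.9 | 0.19 | 0.20 | 5.26 | 1.05 | 23% |

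Worked for r = 0.8: 1 − 0.64 = 0.36 and 1/0.36 = 2.78; 2 × 0.2 = 0.40 and 0.40/0.36 = 1.11. The last column is Φ((1.96 + 0.84)√(1 − r²) − 1.96).

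The two readings move in opposite directions. As r rises, the loss grows if 12-week values are compared and shrinks if changes are compared. ANCOVA is at least as precise as either at every r. Any further gain from the minimisation variables is not counted, and the rank tests were not computed separately.

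**Scale and test.** These points need no arithmetic. Trial assessments calculates continuous quantities from bioimpedance, while Table 3 calls bioimpedance ordinal. The row's hypothesis is between arms, while the signed-rank test works within participants.

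**The case against.** A reader might infer that the plan throws the baseline value away and so loses up to a factor of five in efficiency. The document does not support that. The outcome is loss over 12 weeks, which is naturally a change from baseline, and Table 3 does not name the variable tested. A t-test or Mann-Whitney test on change uses baseline, and so does the signed-rank test. The 1.33 to 5.26 range applies only if 12-week values alone are compared. If muscle measures correlate strongly within a person, which the document neither states nor quantifies, a test on change loses little.

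It can also be said that Table 3 offers only possible methods, that a detailed SAP will follow, and that an unadjusted comparison in a randomised trial is valid. Validity stands: the issue is efficiency. The deferral stands in part. A SAP may supply the missing detail, but the table's footnote presents these as the methods that will be applied, and the text refers to the table for the other secondary outcomes. An ordinal label and a paired test are stated choices, not omitted detail.

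Two further cautions hold. The row was flattened on extraction, so the pairing of the t-test with grip strength and the rank tests with bioimpedance is inferred from order. No pairing, however, turns signed ranks into a between-arm test or adds a covariate. Nor does anything say that within-arm p-values will be set against each other; Mann-Whitney is listed for the comparison of arms. Mann-Whitney is also valid for continuous data, so the ordinal label in itself costs little validity.

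**Conclusion.** The point holds as a minor one. Table 3 names unadjusted tests for two measures taken at baseline and 12 weeks, leaves open whether values or changes are compared, mislabels bioimpedance as ordinal, and lists a paired test that cannot address its own hypothesis. The between-arm tests remain valid but are less efficient than a baseline-adjusted analysis. Under the assumed r of 0.5 to 0.9 and equal variances, the cost is 1.33 to 5.26 times the participants if 12-week values are compared, and 1.33 falling to 1.05 times if changes are compared. The scale label and the signed-rank test need correcting under either reading. Only secondary outcomes in a subset of centres are affected; the primary analysis is untouched.

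**What to change.** In the Function row of Table 3 and in the SAP:

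1. Analyse 12-week grip strength, muscle mass and skeletal muscle index by ANCOVA, with terms for arm, the participant's baseline value of the same measure, and the minimisation variables (age group, fracture type, frailty group). Transform the outcome or use robust standard errors if it is skewed.
2. Relabel bioimpedance as continuous and name the derived quantities as the outcomes.
3. Remove the Wilcoxon signed-rank test as a treatment comparison. If within-arm change is shown, report it descriptively.

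The cost is one table row and the matching SAP text. No new data are needed, because the baseline measurement is already scheduled. The change should be made before the SAP is finalised.

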### Aims and objectives

The primary aim is to determine the difference in QoL measured using the EQ-5D-5L (EuroQol 5 dimension instrument with 5 levels) at 12 weeks between frail or older patients with odontoid process fractures managed with a hard collar (standard care) or without any immobilisation (intervention).

Secondary aims include assessing differences in neck pain, functional recovery, complications, radiological findings, mortality and overall healthcare use and costs, up to 1 year postinjury.

A nested qualitative study will explore trial recruitment experiences from the perspectives of patients, carers, and healthcare professionals, and explore adherence to group allocation. Findings from the qualitative study will inform recruitment and consent procedures and aid interpretation of trial results.

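### The mortality analysis in Table 3 lists an unadjusted chi-squared test, and a logistic regression with no stated adjustment, although allocation is minimised on age, frailty and fracture type

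*Protocol article*

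**What the plan says.** All references are to the protocol article.

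- **Randomisation and interventions.** Allocation uses minimisation with probability 0.8 on age (below 75 or not), fracture type (I to III) and CFS (below 5 or not).
- **Data analysis plan, Table 3, Mortality row.** The outcome is "All-cause mortality (binary)" and the methods are "Logistic regression, Χ^2". The row has no time point, does not say which method leads, and states no adjustment.
- **Table 3, other rows.** The EQ-5D-5L row and the repeated-measures entry in the Function row both state adjustment for the minimisation factors. The table is titled "Possible methods of analysis", while its footnote describes the contents as the methods that will be used. A detailed analysis plan is promised.
- **Outcome measures.** Mortality appears once: "Six and 12 months: EQ-5D-5L, NDI, Neck Numeric Pain Scale, injury-related complications, mortality". The 12-week list, which begins "Twekve weeks: NDI, Neck Numeric Pain Scale, adverse events (AEs), compliance with hard collar use, analgesia use, length of hospital stay, discharge destination", does not contain it.
- **Trial assessments, Table 1.** Mortality is marked at 12 weeks, 6 months and 12 months, timed from randomisation. The table is introduced with "Assessments and timing of data collection are shown in table 1".
- **Aims and objectives.** The horizon for the secondary aims is "mortality and overall healthcare use and costs, up to 1 year postinjury".

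**The concern.** Minimisation makes the arms more alike on age and frailty than chance would. If those factors predict death, the true variance of the difference in death rates is smaller than the variance that a chi-squared test assumes. The test then rejects less often than its nominal 5% under no effect and has less power than a model containing the factors. The article follows the right principle for the primary outcome but not for mortality.

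The stakes are modest but real. The Introduction puts one-year mortality at 20% to 50%, mortality is a secondary outcome named in the abstract, and Table 3 states a hypothesis of no difference. A needlessly insensitive test makes no difference easier to report.

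A binary death variable also needs a horizon and a time origin, and the row gives neither.

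**Working it through.** **Plan figure.** The article gives no event count or power for mortality, so there is none to reproduce. The only figure used is the total of 887, which does follow from the stated steps: 1514/0.8 = 1892.5, rounded to 1893, and 1893 × 0.75 × 0.625 = 887.3.

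**Assumptions not in the article.** One-year mortality 32%; hazard ratios for death of 2.2 (age ≥75) and 2.7 (CFS ≥5); 75% aged ≥75 and 50% with CFS ≥5, independent of each other; constant hazards; no loss to follow-up. Fracture type is taken as not prognostic in the formula.

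**Step 1: share of outcome variance explained.** A baseline hazard of 0.1167 per year gives 32% overall. Risk is 1 − exp(−0.1167 × hazard ratio).

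| Stratum | Weight | 12-month risk |
|---|---|---|
| <75, CFS <5 | 0.125 | 0.110 |
| ≥75, CFS <5 | 0.375 | 0.226 |
| <75, CFS ≥5 | 0.125 | 0.270 |
| ≥75, CFS ≥5 | 0.375 | 0.500 |

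The between-stratum variance is 0.0213 and the total variance is 0.32 × 0.68 = 0.2176, so R² = 0.098.

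**Step 2: size of the chi-squared test.** If the factors are fully balanced, the true variance of the difference is about (1 − R²) times the variance assumed. Null rejection ≈ 2{1 − Φ(1.96/√(1 − R²))} = 2{1 − Φ(1.96/0.950)} = 2{1 − Φ(2.063)} = 3.9%.

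**Step 3: power when one arm's hazard is 1.4 times the other's.** The risks become 0.320 and 0.410, a difference of 0.0896. The mean risk is 0.365, so SE = √(0.365 × 0.635 × 4/887) = 0.0323 and the ratio is 2.77. R², recalculated from the averaged stratum risks, is 0.109.

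- Unadjusted: Φ((2.77 − 1.96)/√0.891) = Φ(0.86) = 80.5%.
- Adjusted: Φ(2.77/√0.891 − 1.96) = Φ(0.98) = 83.6%.

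**Step 4: simulation of the 12-month tests, n = 887.** The first three rows use minimisation at 0.8 on the three factors, with factor prevalences and prognostic effects assumed.

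| Setting | Null: chi-squared | Null: adjusted | Power: chi-squared | Power: adjusted |
|---|---|---|---|---|
| 32% mortality (10,000 null, 4,800 effect trials) | 3.8% | 4.9% | 81% | 84% |
| 32% mortality, separate run (10,000 null) | 3.9% | 5.05% | – | – |
| About 42% mortality | 3.7% | 5.2% | 87% | 90% |
| No minimisation, 20% mortality (1,500 each) | 4.9% | 5.0% | 54% | 57% |
| No minimisation, 50% mortality (1,500 each) | 4.8% | 4.9% | 65% | 68% |

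Power is at a treatment hazard ratio of 1.4 in the minimised rows. In the last two rows it is at an odds ratio of 1.4, with odds ratios of 2 (age) and 2.5 (CFS). The Monte Carlo standard error at 5% with 10,000 trials is √(0.05 × 0.95/10,000) = 0.22 points, so 3.8% to 3.9% is a real departure from 5%. Without minimisation the conservatism disappears, which identifies its cause. The power gain from adjustment remains at about 3 points.

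**Step 5: dates side by side.** The outcome list gives 6 and 12 months. Table 1 gives 12 weeks, 6 months and 12 months. Table 3 gives no date. The first two agree on 6 and 12 months, so the one direct mismatch is the status of 12 weeks. On origin, Table 1 counts from randomisation and the aims sentence from injury, with up to 3 weeks allowed between the two.

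**The case against.** The strongest reply is that Table 3 is titled "Possible methods of analysis" and that an analysis plan, not shown here, will make the choice. That stands in part: leaving the date and the lead method open in a condensed article is not a fault in itself. The footnote does, however, present the listed methods as those to be used, and one of them cannot use the factors on which the trial balances its arms. Adjustment is written into other rows of the same table but not this one.

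A second reply is that logistic regression and chi-squared do not conflict for a binary outcome and that the loss is small. Both points are correct. Taking whichever of the two is significant at 12 months rejected in 5.1% of null trials with minimisation, so listing both causes essentially no inflation.

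A reader might go further and infer that the mortality or safety result depends on which part of the article is followed. The text does not support this. Table 1, "Timing of study assessments", is a collection schedule, and recording deaths at 12 weeks does not make them a tested outcome. The aims sentence is a general horizon for a list of outcomes. The article does not call mortality its safety result. Lower power at 12 weeks than at 12 months only reflects fewer deaths by then.

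A reader might also compute a multiple-testing error of about 11% to 12% by taking the best of chi-squared at three dates and adjusted logistic regression at 12 months. Nothing in the article commits the trial to that rule.

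**Conclusion.** The point holds as a modest improvement to the mortality analysis, not as an error that threatens the trial. With minimisation and the assumed prognostic effects, the unadjusted chi-squared test runs at about 3.7% to 3.9% instead of 5% and loses about 3 points of power (80.5% against 83.6% by formula; 81% against 84% and 87% against 90% by simulation). The size rests on hazard ratios and prevalences that the article does not give. Weaker prognostic effects would shrink it, and with none it would vanish.

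The 12-week discrepancy between the outcome list and Table 1 is a genuine but minor inconsistency. Neither matter touches the primary outcome or the sample size.

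**What to change.** In the Mortality row of Table 3, delete chi-squared and specify logistic regression adjusted for age, CFS and fracture type. In the same row, name the time point or points and state that time runs from randomisation. In Outcome measures or under Table 1, say whether 12-week mortality is an outcome or only collected. Which of the listed dates to test is for the trial team to decide; this point does not require 12 months to be the only one.

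The cost is wording only, because the covariates are already recorded for the minimisation. The reported odds ratio becomes conditional on those covariates, so deaths and percentages by arm should be shown beside it.
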